### Sample size calculation

The sample size was based on the primary outcome of a change in baseline eGFR. To determine the sample size, we reviewed unpublished data for eGFR changes for 22 ADPKD outpatients at CKD stages III–IV. The mean value of eGFR was 26.71 mL/min/1.73 m^2^, and the standard deviation was 8.53 mL/min/1.73 m^2^. It was assumed that eGFR for the YNF group would be significantly higher than for the control group by more than 6 mL/min/1.73 m^2^ after 24 weeks. If α = 0.05 and the test efficacy 1 – *β* = 0.80, then the sample size$$ {n}_1=\kern0.5em \kappa {n}_2 $$

where$$ {n}_2=\frac{\left({\mathrm{Z}}_{\alpha /2}+{\mathrm{Z}}_{\beta}\right){}^2\kern0.5em \sigma {}^2\kern0.5em \left(1\kern0.5em +\kern0.5em 1/\kappa \right)}{\varepsilon^2}. $$

Thus, *n*_1_ = 64, with 32 in each treatment group. Considering a 10% dropout rate, the planned sample size for randomization was increased to 72. Participants will be randomly assigned in a ratio of 1:1. Each of the three participating hospitals will recruit 24 patients, 12 in the experimental group and 12 in the control group.

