### Randomization

The central randomization list was generated by an independent statistician using SPSS (version 24.0, IBM, NY, USA). Altogether, 36 patients will be assigned to the intervention group and to the control group using a balanced block randomization with 6 blocks. We will randomly select blocks of size 4. Telephone-based randomization will be performed at each coordinating center by an independent physician who is not engaged in recruitment, treatment, or assessment. Participants will be randomly assigned in each site to the YNF group and the placebo group in a ratio of 1:1. After screening, if the patient agrees to participate and voluntarily signs the informed consent form (Additional file 2), the independent physician in each trial site will sequentially assign a random number to them.

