### Measurement items and time points of data collection

Relevant examinations will be performed to collect patient data at 24 weeks before baseline, at baseline, every 4 weeks from 4 to 24 weeks during treatment, and an additional follow-up evaluation will be performed at visit 9 (48 weeks). General information collected will include name, age, gender, ID number, date of birth, home address, contact information, history of present illness, past medical history, family history, personal life history, menstrual history, marital history, allergy history, social history, physical examination results, and laboratory examination results.

There is evidence that age-related TKV can reflect the progress of ADPKD. An MRI scan can accurately measure renal blood flow and evaluate renal cyst compression, which is associated with pain, hypertension, hematuria, albuminuria, and loss of renal function. TKV combined with age and renal function can be used to evaluate the risk of progress to ESRD [19]. The T2 shortening imaging technique of MRI with no radiation damage, no use of gadolinium as a contrast agent, and no risk of nephrogenic systemic fibrosis is recommended and will be used in this study [20]. The outcome is the percentage semi-annual change in TKV measured by MRI, which will be performed at visit 1, visit 2 (24 weeks after visit 1), and visit 8 (24 weeks after visit 2) to observe the growth in kidney volume before and after the intervention.

Items to be measured and the time points of data collection are listed in Table 2.

**Table 2 Tab2:** SPIRIT table: Measurement items and time points of data capture

Items	Screening	Baseline	Treatment						Follow-up
	Visit 1	Visit 2	Visit 3	Visit 4	Visit 5	Visit 6	Visit 7	Visit 8	Visit 9
	−24 weeks	0 weeks	4 weeks	8 weeks	12 weeks	16 weeks	20 weeks	24 weeks	48 weeks
General									
Informed consent	×								
Inclusion and exclusion criteria	×								
Collect general information	×								
General physical examination	×								
Urine hCG (only women)	×								
Medical and drug use history	×								
Concomitant disease and treatment	×								
Combined medication	×	×	×	×	×	×	×	×	×
Effectiveness observation									
Vital signs	×	×	×	×	×	×	×	×	×
TCM symptoms	×	×	×	×	×	×	×	×	×
Pain evaluation	×	×	×	×	×	×	×	×	×
Renal function (eGFR, Scr, BUN)	×	×	×	×	×	×	×	×	×
MRI (TKV)	×	×						×	
Blood electrolytes	×	×			×			×	×
Urine β2-MG, mALB/Cr, RBP	×	×						×	×
Safety observation									
Blood test ^#^	×	×			×			×	×

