### Outcomes

The primary outcome of this trial will be the eGFR using the CKD Epidemiology Collaboration formula [21]. Secondary outcomes include changes in TKV, Scr, blood urea nitrogen (BUN), TCM symptoms, and pain. A composite outcome looks at the incidence rates of all possible safety events between two groups. AEs will be monitored throughout the trial and several biological indicators (blood and urine tests, electrocardiograms, and liver function test) will also be closely watched.

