### Statistical analysis

A formal and detailed statistical analysis plan will be formulated before the database is locked. The baseline characteristics of both groups, such as gender, age, and smoking status, will be compared by either a χ^2^ test or Student’s *t*-test. Continuous variables will be presented as means ± standard deviations or medians, and differences in such variables will be analyzed using an independent *t*-test or the Wilcoxon signed-rank test. A repeated measurement of variance analysis model of these outcomes will be built.

The difference in eGFR will be tested using two-way ANOVA with repeated measures. Categorical variables will be expressed as numbers and percentages, and differences in such variables will be calculated and compared using a χ^2^ test and Fisher’s exact test. All statistical tests will be two-sided, and the level of significance will be set to *P* < 0.05. Multiple imputation will be used to handle missing data. All patients enrolled will be included in the primary analysis in accordance with the intention-to-treat principle. The statistical analysis will be performed in a blind manner by an independent statistician using SPSS (version 24.0, IBM, NY, USA). No additional analyses or an interim analysis are scheduled.

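### The planned eGFR test, a two-way repeated-measures ANOVA, has no standard term equal to the 24-week difference that the trial is sized on, and no deciding term, contrast or adjustment is named

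*Protocol article*

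**What the plan says.** Four parts of the protocol article bear on this.

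- **Outcomes** names the measure without a time point: "The primary outcome of this trial will be the eGFR using the CKD Epidemiology Collaboration formula".
- **Sample size calculation** supplies both a measure and a time point. It says "The sample size was based on the primary outcome of a change in baseline eGFR", and it assumes the YNF group will be "significantly higher than for the control group by more than 6 mL/min/1.73 m^2^ after 24 weeks". The formula is the usual one for comparing two means.
- **Statistical analysis** gives the test: "The difference in eGFR will be tested using two-way ANOVA with repeated measures". It does not say which term decides, which visits enter, or whether baseline eGFR or site is in the model. The same section defers detail to an analysis plan to be written before database lock.
- **Randomization** balances allocation within hospital: "Participants will be randomly assigned in each site to the YNF group and the placebo group in a ratio of 1:1".

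In Table 2 the row "Renal function (eGFR, Scr, BUN)" is marked at all nine visits: weeks −24 and 0, six visits from week 4 to week 24, and week 48, which is 24 weeks after treatment ends.

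**The concern.** A two-way (group by time) repeated-measures ANOVA gives two tests that involve treatment. The group main effect compares the arms on their average over whichever visits are included. The group × time term asks whether the two profiles differ in shape anywhere. The trial is sized on a third quantity, the gap between the arms at week 24.

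The trial's one confirmatory p-value could therefore answer a different question from the one it was designed for. The main effect may miss a real 24-week benefit because earlier visits dilute it. The interaction may be significant when the arms do not differ at week 24. Because the deciding term is not named, the choice could also be made after results are seen.

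**Working it through.** **The plan's own figure.** Inputs from Sample size calculation: difference 6, SD 8.53, α 0.05 (two-sided, per Statistical analysis), power 0.80, allocation 1:1.

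n per arm = 2 × (1.960 + 0.842)² × 8.53² / 6² = 31.7, so 32 per arm and 64 in total. With 10% dropout, 64 / 0.9 = 71.1, so 72. The stated figures reproduce. A t-test of the week-24 difference with 32 per arm has 79% power (noncentral t, 62 df).

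**Assumptions for the rest.** The article gives neither the within-patient correlation ρ nor the time course of the effect. I take ρ from 0.7 to 0.9, compound symmetry, seven visits (weeks 0 to 24), 32 per arm, and 8.53 as the SD of eGFR at each visit.

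**Group main effect.** The SD of a patient's seven-visit mean is 8.53 × √[(1 + 6ρ)/7], which is 7.35 at ρ 0.7 and 8.16 at ρ 0.9. The standard error of the difference is that SD × √(2/32), which is 1.84 to 2.04.

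| True effect, weeks 0 to 24 | Average difference | Power, ρ 0.7 | Power, ρ 0.9 |
|---|---|---|---|
| Linear rise 0, 1, 2, 3, 4, 5, 6 | 21/7 = 3.0 | 36% | 31% |
| Constant 6 from week 4 | 36/7 = 5.14 | 79% | 70% |

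Both rows have the same true week-24 difference of 6.

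**Group × time.** The noncentrality is (32/2) × Σ(eₜ − ē)² / [8.53² × (1 − ρ)], where eₜ is the true difference at visit t and ē its average, with 6 and 6 × 62 = 372 df.

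| True effect, weeks 0 to 24 | Σ(eₜ − ē)² | Noncentrality, ρ 0.7 | Significant, ρ 0.7 | Significant, ρ 0.9 |
|---|---|---|---|---|
| Linear rise to 6 | 28.0 | 20.5 | 94% | >99% |
| Transient 0, 4, 6, 6, 4, 2, 0 | 38.9 | 28.5 | 99% | >99% |

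The second row has no week-24 difference, yet it is declared significant at least as often as the first. If the week-0 visit is left out and the effect is a constant 6 from week 4, the profiles are parallel and group × time has only its 5% type I error rate.

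**Baseline-adjusted week-24 comparison.** The result depends on what 8.53 measures.

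- As the SD of levels, the residual SD is 8.53 × √(1 − ρ²), which is 6.1 (ρ 0.7), 5.1 (0.8) or 3.7 (0.9). Power is 97%, 99.6% and over 99.9%.
- As the SD of change, the residual SD is 8.53 × √[(1 + ρ)/2], which is 7.9 (ρ 0.7) to 8.3 (ρ 0.9). Power is 85% to 81%.

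The article does not settle which reading applies. It says eGFR changes were reviewed, but gives "the standard deviation was 8.53 mL/min/1.73 m^2" beside a mean of 26.71, which looks like a level.

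**The case against.** The best defence is that the article promises a detailed analysis plan, and that contrasts, visits and covariates are commonly fixed there. The sample-size section already gives week 24 as an anchor. Silence on covariates is therefore not an error in itself. What remains is that the article does fix a method for eGFR, and an analysis plan that follows it literally inherits the mismatch.

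Several stronger readings are tempting, and the documents do not support them.

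- *That the analysis ignores baseline eGFR.* The text does not say so. If Visit 2 is a level of the time factor, group × time measures divergence from baseline; if change scores are modelled, baseline enters directly. All that can be said is that no baseline covariate is named.
- *That all nine visits enter the model.* Table 2 shows when eGFR is measured, not what is analysed. Power figures built on the pre-treatment and week-48 visits would rest on a model that the article does not state.
- *That the test is simply underpowered.* This holds only for the main effect, and strongly only if the effect builds slowly. Group × time is well powered for the same linear rise. Its weakness is that it does not isolate week 24.
- *That omitting site invalidates the result.* After balanced allocation within site, leaving site out does not bias the estimate. It usually makes the test slightly conservative. No between-site variance is given, so the loss cannot be computed.

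**Conclusion.** The concern holds in this limited form: the named test and the sizing address different quantities, and nothing in the article says which term or contrast decides. For a true week-24 difference of 6, main-effect power ranges from 31% to 79% according to the time course and ρ. The interaction detects the linear rise with 94% power or more, but is significant just as readily when the week-24 difference is zero. These figures rest on the assumed ρ, compound symmetry, the assumed time courses and 8.53 as the SD of levels.

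The sample-size arithmetic is correct, and 72 patients suffice for the analysis proposed below. The benefit of baseline adjustment may be large (79% to at least 97%) or small (79% to about 81–85%), depending on what 8.53 represents. The case for the change does not depend on that gain. It rests on making the confirmatory test answer the question that the trial was sized for.

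**What to change.** Replace the eGFR sentence in Statistical analysis, and carry the same text into the analysis plan, along these lines:

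*The primary analysis estimates the treatment difference in eGFR at Visit 8 (week 24), with its 95% confidence interval. It uses a repeated-measures mixed model on the on-treatment visits (Visits 3 to 8) with treatment, visit, treatment × visit, Visit 2 eGFR and site. Visit 9 is analysed separately as an off-treatment secondary outcome.*

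An ANCOVA of Visit 8 eGFR on treatment, Visit 2 eGFR and site is an acceptable simpler alternative. One of the two should be chosen in advance. Outcomes should give the same time point. Using the same form for the secondary outcomes is optional.

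The cost is wording only. No visits, measurements or patients are added, the analysis plan is still to be written, and the software named in the article can fit either model.

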Chinese herbal medicine has been used in the treatment of diseases for thousands of years in China. It is well known that traditional Chinese medicine (TCM) cures ailments based on syndrome differentiation, which is the main characteristic and therapeutic rule of TCM. Clinical information is gathered using the four main diagnostic TCM procedures (observation, listening, interrogation, and pulse-taking) and diagnosis follows TCM criteria. With our many years of clinical practice in the management of ADPKD, we have found that the main pathogenesis of ADPKD is spleen and kidney deficiency (soreness and weakness of the waist and knees, fatigue, cold or numbness of limbs, mental listlessness, lower limb edema, frequent night urination, and sunken pulse) combined with blood stasis (abdominal mass, pain or tingling in the back, subcutaneous petechia, squamous and dry skin, chest tightness, dark purple or dull red tongue with white fur, and strong astringent pulse). The clinical terms for these symptoms are those used in TCM for diagnosis and treatment. The national standard in China for this syndrome was published in February 1997 [13] and was verified by our previous work [14].

The *yinang* formulation (YNF) is derived from a Chinese patent drug originally designated for the clinical treatment of ADPKD patients diagnosed with the spleen, kidney deficiency, and blood stasis syndrome [14]. However, it is not clear whether YNF is effective for ADPKD patients with chronic kidney disease (CKD) stages III–IV. We hypothesized that for patients with ADPKD, YNF could improve the estimated glomerular filtration rate (eGFR), improve serum creatinine (Scr) levels, reduce TKV, reduce the blood pressure, improve symptoms and signs of CKD, reduce ADPKD-related pain, and reduce the number of adverse events (AEs). Thus, a multi-center prospective double-blind placebo-controlled randomized clinical trial was designed to evaluate the safety and efficacy of YNF for CKD stages III–IV in ADPKD patients.

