### Measurement scale for TCM symptoms

The measurement scale for TCM symptoms recommended by the *Guidelines for Clinical Research of Chinese Medicine (New Drug)* [16] will be used for ease of assessment. Each of the primary symptoms necessary for the diagnosis of the spleen, kidney deficiency, and blood stasis syndrome will be scored 0, 2, 4, or 6, while secondary symptoms will be scored 0, 1, 2, or 3. The scores will be summed to yield a total score for each set of symptoms for each patient. The total primary symptom score cannot exceed 18 and the total score for secondary symptoms cannot exceed 33 for a patient. The two totals will be added together and any change in this score will be calculated for each patient and used to calculate an efficacy indicator (EI) for the evaluation of treatment efficacy:$$ \mathrm{EI}=\left(\mathrm{Total}\ \mathrm{symptom}\ \mathrm{score}\ \mathrm{at}\ \mathrm{baseline}-\mathrm{Total}\ \mathrm{symptom}\ \mathrm{score}\ \mathrm{post}-\mathrm{treatment}\right)/\mathrm{Total}\ \mathrm{symptom}\ \mathrm{score}\ \mathrm{at}\ \mathrm{baseline}\times \kern0.37em 100\% $$

The degree of symptom improvement will be presented in four categories ranging from full recovery (EI ≥ 90%), good recovery (90% > EI ≥ 70%), and modest recovery (70% > EI ≥ 30%) to no recovery (EI < 30%).

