### Pain evaluation scale

Pain is the most common complaint of patients with ADPKD. Causes of pain are multiple but include cyst enlargement, cyst rupture, and secondary infection [22]. Good remission of ADPKD-related pain (low back pain, abdominal pain, headache, chest pain, and leg pain) can alter a patient’s quality of life. The visual analog scale (VAS) is a 10-cm horizontal line anchored by two extremes. It will be used to measure ADPKD-related pain [23]. Patients will be instructed to complete a pain diary for the day at each visit. According to this scale, 0 cm means no pain or no discomfort, whereas the 10-cm end indicates the worst pain or extreme discomfort. The baseline will be the VAS score at visit 2. The difference in pre- and post-treatment VAS scores will be a secondary outcome. At the final visit, patients will complete a global assessment of their overall responses after the trial. The global assessment [24] is a five-point scale: 0 = worsened, 1 = no change, 2 = slightly improved, 3 = improved, and 4 = significantly improved.

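### The only tests named for categorical variables ignore order, yet the two graded response scales (four symptom-recovery categories and a 0-4 global assessment) are ordered

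*Protocol article*

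**What the plan says.** Four places in the protocol article bear on this.

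- **Statistical analysis.** The rule for categories names χ² and Fisher's exact tests: "Categorical variables will be expressed as numbers and percentages, and differences in such variables will be calculated and compared using a". Continuous variables get an independent t-test or the Wilcoxon signed-rank test, and a repeated-measures model is planned. "All statistical tests will be two-sided, and the level of significance will be set to" P < 0.05. The section defers detail to a formal analysis plan to be written before database lock.
- **Measurement scale for TCM symptoms.** A total symptom score is formed, and its percentage fall from baseline is the EI. Then: "The degree of symptom improvement will be presented in four categories ranging from full recovery" down to no recovery, with cuts at 90%, 70% and 30%.
- **Pain evaluation scale.** Pain is a numeric visual analogue score. At the final visit patients also complete a global assessment, a "five-point scale: 0 = worsened, 1 = no change, 2 = slightly improved" and so on up to 4.
- **Background.** The stated hypothesis has a direction: YNF could "improve symptoms and signs of CKD, reduce ADPKD-related pain", among other benefits.

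The Outcomes section lists changes in TCM symptoms and in pain as secondary outcomes. It does not list the global assessment.

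**The concern.** Both graded scales run from worse to better, and the question is whether patients on YNF sit higher on them. Pearson χ² and Fisher's exact test on a 2 × 4 or 2 × 5 table do not use that ordering. They ask whether the two distributions differ in any way, and χ² spreads the evidence over 3 or 4 degrees of freedom. Two things follow. A true upward shift is missed more often than it need be. And a significant result does not by itself show that more patients improved, since a difference in spread alone can produce it.

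The section names no between-arm test that would serve instead. The only rank method mentioned, the signed-rank test, is for paired data and cannot compare two independent arms.

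The question here is about order, not about one-sided testing. A two-sided test that uses order keeps the protocol's two-sided 5% level.

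**Working it through.** **1. The plan's own figure.** Inputs from Sample size calculation: α = 0.05 two-sided, power 0.80, SD 8.53, difference 6, equal arms.

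n per arm = (1.960 + 0.842)² × 8.53² × 2 / 6² = 31.7, so 32 per arm and 64 in all. Then 64 / 0.90 = 71.1, rounded up to 72, or 36 per arm. The protocol's 64 and 72 reproduce. They concern eGFR only; no power is stated for either ordered scale.

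**2. Assumptions.** The protocol gives no category proportions and no effect for these scales, so both are assumed. The treated distribution is an ordered shift: at each cut, the odds of being at or below that level equal the control odds divided by a common odds ratio (OR). For example, control 50/35/12/3% (none to full recovery) with OR 3:
- cumulative 0.50: odds 1.00 / 3 = 0.333, giving 0.250
- cumulative 0.85: odds 5.67 / 3 = 1.89, giving 0.654
- cumulative 0.97: odds 32.3 / 3 = 10.8, giving 0.915

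so the treated arm is 25.0/40.4/26.1/8.5%.

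**3. Power under an ordered shift.** Simulation, 40,000 trials per cell, two-sided 5%, Pearson χ² against the tie-corrected rank-sum test. One control distribution per scale is shown: 50/35/12/3% for four levels and 10/40/30/15/5% for five.

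| Levels | n per arm | OR | χ² | Rank-sum | Gain (points) |
|---|---|---|---|---|---|
| 4 | 32 | 1.5 | 9% | 14% | 5 |
| 4 | 32 | 2 | 19% | 31% | 12 |
| 4 | 32 | 3 | 46% | 64% | 19 |
| 4 | 32 | 4 | 68% | 84% | 16 |
| 4 | 36 | 1.5 | 9% | 15% | 6 |
| 4 | 36 | 2 | 21% | 34% | 13 |
| 4 | 36 | 3 | 51% | 70% | 18 |
| 4 | 36 | 4 | 74% | 88% | 14 |
| 5 | 32 | 1.5 | 8% | 14% | 6 |
| 5 | 32 | 2 | 17% | 33% | 16 |
| 5 | 32 | 3 | 42% | 66% | 25 |
| 5 | 32 | 4 | 64% | 85% | 22 |
| 5 | 36 | 1.5 | 9% | 15% | 7 |
| 5 | 36 | 2 | 19% | 36% | 17 |
| 5 | 36 | 3 | 48% | 73% | 25 |
| 5 | 36 | 4 | 70% | 89% | 19 |

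Gains are taken before rounding. Over several control distributions the gain at OR 2 to 4 is about 12 to 18 points (four levels) and 15 to 24 (five levels). Including very skewed controls widens this to roughly 10 to 19 and 15 to 26. At OR 1.5 it is about 4 to 7. Against the exact (Fisher-Freeman-Halton) test at 32 per arm and OR 2 to 4, the gains are 7 to 18 and 11 to 23.

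As a cross-check, at equal noncentrality the largest gap between a 1-df test and a 3-df test is 17.0 points, and between 1 df and 4 df it is 21.8. The simulated gains are of that order.

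**4. Differences that are not a shift, 36 per arm.**

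| Comparison | χ² | Rank-sum |
|---|---|---|
| 10/40/40/10 v 25/25/25/25 (spread only) | 61% | about 5% |
| 5/25/40/25/5 v 15/20/30/20/15 (spread only) | about 33% | about 5% |
| 40/30/20/10 v 40/5/45/10 | about 80% | about 16% |

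The first two rows show χ² responding to spread with no net improvement. The third shows χ² doing much better when patients move between two adjacent levels only.

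**The case against.** Four points can be made for the plan, and each has some force.

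*The protocol never says that these two scales go to χ² or Fisher.* True. A reader might infer an explicit assignment, but the recovery levels are only said to be presented, and no test is named for the global assessment. The application follows from the general rule. It still stands as a point, because the rule covers all categorical variables, makes no exception for ordered ones and offers no alternative.

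*The listed TCM outcome is already numeric.* The change in total score and the EI are numbers and fall under the rule for continuous variables, as does the pain score. The global assessment is not a listed outcome. A reader might infer that a named secondary outcome is lost to a weak test. The document does not support that, and this limits the reach of the point. But it does not say outright whether the number or the categories carry the TCM comparison.

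*The loss can be exaggerated.* A reader might set a t-test on the uncut EI against χ² on its four categories. With an assumed control mean of 20, SD 25, a shift of 0.67 SD and 36 per arm, the t-test has 80%, the rank-sum test on the categories 65% and χ² 47%. Of the 33 points, about 18 (65 − 47) come from ignoring order and 15 (80 − 65) from cutting the score. The whole gap is not the cost of the χ² test.

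*χ² is a valid test and sometimes the better one.* Also true. Rejecting when spread differs is correct for its own null, not a false positive. The objection to it is that its null is not the protocol's question.

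**Conclusion.** The point holds as a minor improvement to secondary analyses. The only tests named for categorical variables ignore order; under that rule the four recovery levels and the 0-4 global assessment would be compared in a way that does not match a hypothesis of more improvement.

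The size rests wholly on assumed proportions and an assumed ordered shift. With OR 2 to 4 and 32 to 36 per arm, using order is worth about 12 to 18 points of power on four levels and 15 to 24 on five. With a weak shift (OR 1.5) it is worth little, and with a non-shift difference the advantage can reverse. Nothing here touches the primary eGFR analysis, the sample size of 72, or the numeric change in symptom score and pain.

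**What to change.** Amend the Statistical analysis section, or carry the change into the analysis plan due before database lock:

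1. Limit χ² and Fisher's exact tests to binary and unordered variables.
2. Compare the ordered scales between arms with the Wilcoxon rank-sum (Mann-Whitney) test, or with a proportional-odds model reporting a common odds ratio and 95% confidence interval. Say rank-sum, not signed-rank.
3. State that the between-arm TCM symptom comparison uses the numeric score change or the EI, with the four categories shown as numbers and percentages.

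The cost is one or two sentences, with no new data or patients. The downsides are less sensitivity to a pure change in spread and, if the model is used, a proportional-odds assumption to check.
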